#### \* Early Treatment Failure (ETF) (one of the following)

- (i) Development of danger signs or severe malaria (see Appendix V) on Day 0, Day 1, Day 2 or Day 3, in the presence of parasitaemia,
- (ii) Parasite density on Day 2 > Day 0 count, irrespective of axillary temperature,

- (iii) Presence of parasitaemia on Day 3 with fever (axillary temperature  $\geq 37.5^{\circ}\text{C}$ ),
- (iv) Parasitaemia on Day 3  $\geq 25\%$  of count on Day 0.

### **\*\* Late treatment failure (LTF)**

LTF is divided in late clinical and late parasitological failure.

#### Late Clinical Failure (LCF):

- (i) Development of danger signs or severe malaria after Day 3 in the presence of parasitaemia, (See Appendix V for the criteria of severe malaria/danger signs).
- (ii) Presence of parasitaemia and fever on any day from Day 4 to Day 28, without having previously meet the criteria of ETF.

#### Late Parasitological Failure (LPF):

Reappearance of parasitaemia after day 3 in the absence of fever (axillary temperature  $<37.5^{\circ}\text{C}$ ) without having previously meet the criteria of ETF or LCF.

The adequate clinical and parasitological response (ACPR) is 1-TF (28 or 63, unadjusted or adjusted). It is defined as absence of parasitaemia at the end of the follow up period (day 28-63), irrespective of axillary temperature without previously meeting any of the criteria of early and late treatment failure. In the adjusted estimates, patients with late asexual parasite reappearance (with or without fever) will be considered ACPR if the PCR analysis shows a new infection rather than a recrudescence.

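### Late parasitological failure covers only reappearance, so afebrile low-density parasitaemia that has not cleared by day 7 meets no failure criterion

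*Protocol*

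**What the plan says.** Section 3.2 defines treatment failure as the sum of early and late failures, citing WHO 2003, and then prints its own criteria.

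- **Early failure (ETF), days 0 to 3.** Danger signs or severe malaria with parasites; "Parasite density on Day 2 > Day 0 count, irrespective of axillary temperature"; "Presence of parasitaemia on Day 3 with fever"; and criterion "iv) Parasitaemia on Day 3" at or above 25% of the day 0 count.
- **Late clinical failure (LCF).** "Development of danger signs or severe malaria after Day 3 in the presence of parasitaemia", or "Presence of parasitaemia and fever on any day from Day 4 to Day 28".
- **Late parasitological failure (LPF).** "Reappearance of parasitaemia after day 3 in the absence of fever", provided neither ETF nor LCF was met earlier.
- **Adequate response (ACPR).** Two statements stand side by side: "The adequate clinical and parasitological response (ACPR) is 1-TF (28 or 63, unadjusted or adjusted"), and "absence of parasitaemia at the end of the follow up period (day 28-63), irrespective of axillary temperature" with no failure criterion met before.

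TF28U counts every failure detected in the first active follow-up. TF28A counts early failures before day 14, plus recurrent parasitaemias from day 14 that genotyping classifies as recrudescence.

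Films are scheduled on days 0 to 3, 7, 14, 21 and 28 (section 3.8, Figure 1). Filter paper is scheduled on days 0 and 1 and from day 14 onwards (section 3.10.1).

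**The concern.** The two late definitions use different words with different scope. LCF needs parasites to be present, but also fever, danger signs or severe malaria. LPF is the only category for afebrile parasitaemia after day 3, and it needs parasites to reappear, which presupposes that they had cleared. A child whose parasites fell below the day 3 threshold but did not clear falls between the two.

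These definitions decide both primary endpoints. They also decide who leaves active follow-up, because section 4.4 acts on the failure classification and section 3.10.2 sorts children into those treated as failures and those who are ACPR. The trial is open label at 10 sites, and section 3.1 promises masked reading only for PCR. Whether an uncleared day 7 film is a reappearance would therefore be decided by staff who may know the allocation, possibly differently from site to site.

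**Working it through.** **1. The written rules applied to example records.** The counts are illustrative: day 0 20,000/µl, day 1 5,000, day 2 3,000. No child has danger signs, and all are afebrile except F on day 7.

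| Case | Day 3 | Later films | Result on the written text |
|---|---|---|---|
| A | 2,000 (10% of day 0) | Day 7 positive; days 14, 21, 28 negative | No ETF, LCF or LPF; ACPR |
| B | 6,000 (30%) | Any | ETF, 25% criterion |
| C | 2,000 (10%) | Day 7 positive, day 14 negative, day 21 positive | LPF on day 21 |
| D | 2,000 (10%) | Positive at every visit to day 28 | No failure criterion met; ACPR by the 1-TF statement, not ACPR by the absence-of-parasites statement |
| E | Negative | Day 7 positive | LPF on day 7 |
| F | 2,000 (10%) | As A, with fever on day 7 | LCF on day 7 |

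A and E have the same films from day 7 onwards. E, who had cleared by day 3, is a failure; A, who had not, is a cure.

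**2. TF28A.** The term early is defined in section 3.2 only for days 0 to 3, so case A is not an early failure on that definition. From day 14 only recurrent parasitaemias count, and case D never recurs. Genotyping could not settle case A either, because no filter paper is scheduled on day 7.

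**3. Does this touch the sample size?** Section 3.5 gives 155 per arm for 90% efficacy, a 10-point margin, 5% significance and 90% power. With a one-sided 5% test:

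n = (1.645 + 1.282)² × 2 × 0.9 × 0.1 / 0.10² ≈ 154.2, rounded up to 155.

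The stated figure is reproduced. It does not depend on the LPF wording.

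**4. Size.** The protocol gives no day 3 or day 7 positivity. Assume that 1% to 5% of children are positive on day 3, and that 5% to 20% of those are still positive and afebrile on day 7 without meeting ETF.

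- Low: 0.01 × 0.05 = 0.05%; 0.0005 × 155 = 0.08 children per arm.
- High: 0.05 × 0.20 = 1%; 0.01 × 155 = 1.55, about 1.6 children per arm.

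**5. Effect on the site comparison if only the worse arm is affected.** Suppose true efficacy is 90% against 80%, and a share q of the worse arm consists of failures scored as cures. The chance of wrongly concluding that the difference is within 10 points is

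Φ(q/SE − 1.645), with SE = √[0.9 × 0.1/155 + (0.8 + q)(0.2 − q)/155].

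- q = 0: 5%.
- q = 0.5%: 6.4%.
- q = 1%: SE = 0.0397, q/SE = 0.252, giving Φ(−1.393) = 8.2%.

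If both arms are affected equally, the hidden failures largely cancel in the difference.

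**The case against.** The strongest reply is that the gap is a residue. ETF already counts three forms of slow clearance: a rise on day 2, any day 3 parasitaemia with fever, and a day 3 count of at least 25% whatever the temperature. LCF catches persistence with fever. A child who clears and turns positive again is LPF (case C). Parasite clearance time is a secondary endpoint in section 3.3. All of this stands. A reader might infer that the primary endpoint leaves out delayed clearance as such, or the clearest sign of a failing drug. The protocol does not support either reading: only low-density, afebrile, uncleared parasitaemia is left out, and nothing in the text ranks that pattern as a sign of drug failure.

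Second, TF28A may be meant more widely than its definition. ETF ends on day 3, so the limit of day 14 adds nothing unless that limb is meant to catch failures on days 4 to 13 without genotyping. That is a plausible reading and would count case A. The gap is therefore less certain for TF28A than for TF28U, and the ambiguity itself needs settling.

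Third, the cited WHO source may be clearer. It is not at hand, and the protocol prints its own operative criteria, so the citation does not close the gap in them.

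Fourth, the frequency is assumed. It is also tempting to say that these children would gather in the slowest-clearing arm. The protocol has no data on that, so step 5 is an illustration and not a forecast.

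**Conclusion.** The point holds in a limited form. An afebrile child with no danger signs, a day 2 count not above day 0, a day 3 count above zero but below 25% of day 0, and a positive day 7 film meets no failure criterion. With negative films from day 14, this child is ACPR and not a failure in TF28U, nor in TF28A unless its first limb is read loosely. A child who never clears and stays afebrile is classified in opposite ways by the two ACPR statements. That child also fits neither group in section 3.10.2, which covers those already treated and those free of infection at day 28. This contradiction does not depend on how often the pattern occurs.

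The number of children affected cannot be derived from the protocol. Under the assumptions shown it is about 0.08 to 1.6 per arm of 155. Within an arm, the error can only lower the failure rate. The sample size stands. The change is worth making because it corrects the rule for both primary endpoints at almost no cost, not because a large bias has been shown.

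**What to change.** The change is to endpoint wording only.

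1. Make LPF cover afebrile parasitaemia that is present or persists after day 3, as well as parasitaemia that reappears, with the existing proviso that neither ETF nor LCF was met earlier. Say whether a film from an unscheduled visit on days 4 to 6 counts.
2. State that a parasitaemia that never cleared is a failure in TF28U and, without genotyping, in TF28A. In the same place, say what early failures before day 14 includes beyond the day 0 to 3 definition.
3. Align the two ACPR statements so that no child can satisfy one and not the other.
4. Reconcile sections 3.10.2 and 4.4 with the corrected definitions, since both depend on the failure classification. The clinical content of those sections is for the protocol's authors.

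Day 7 films are already scheduled, so no new data are needed. The only price is that failure rates may look very slightly less favourable.

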### **3.3 Secondary Endpoints**

The secondary endpoints will be:

- PCR unadjusted treatment failure up to day 63 (TF63U): TF28U plus all recurrent parasitaemias (symptomatic or asymptomatic) detected between day 29 and day 63 by passive follow up, regardless of genotyping.
- PCR adjusted treatment failure for the whole period of passive surveillance (TFAPS): TF28A plus all episodes of recurrent parasitaemia identified as recrudescence by genotyping.
- Fever clearance time (FCT): Fever clearance time will be defined as the time (in days) from the time of randomization to the first two consecutive measurements on 2 different days of axillary temperature below  $37.5^{\circ}\text{C}$ .
- Asexual parasite clearance time (PCT): Asexual parasite clearance time will be defined as the time (in days) from time of randomization to 2 consecutive negative blood slides (collected at different days). The time to the event will be taken as the time to the first negative slide.
- Gametocytaemia (prevalence and density) at day 7, 14, 21 and 28 after treatment (for both active follow-ups);

- Hb changes day 3, 7, 14 and 28 (first and second follow up);
- Clinical malaria after first active follow-up;
- Clinical malaria after second active follow-up;
- TF second clinical episode (D28 and D63);
- DHFR mutations at day 0 first follow-up and day re-appearance of parasitaemia (for patients treated with CDA).
- Safety profiles: Subjects will be monitored for 28 days (first and second follow up) for possible development of adverse events. All adverse events will be recorded on the specific form in the CRF. Vital signs, blood chemistry and haematology will be monitored and changes in relevant laboratory parameters will be assessed.

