## *Methodology*

A multicentre, phase IV, randomized, open label, multi-arm study. Each patient will be actively followed for 28 days and then passively until 6 months after treatment. If, during the passive follow up, the patient experiences a second uncomplicated malaria episode, s/he will be treated with the same drug and actively followed up for additional 28 days.

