All medication will be administered under observation by an authorised member of the study team (physician, clinician, or study nurse).

After the child has reached a study outcome, before or at the end (day 28) of the first active follow up, the parents or guardians will be encouraged to attend the health facility when the child is sick. If the child is not diagnosed with clinical malaria, s/he will be treated accordingly and parents or guardians will be asked to come back again whenever the child is sick. If the child has clinical malaria and meets the inclusion/exclusion criteria, s/he will be treated with the same drug received at the beginning of the first follow up and actively followed for 28 days according to the procedure outlined above. Re-treatment with the same study drug will be done at an interval of at least 29 days from the first treatment, i.e. after the first active follow up has finished. At the end of this second follow up, when one of the study

outcomes is reached, the child will be passively followed up until completion of the 6-month period started at the end of the first active follow up. Any malaria episode will be recorded and the patient treated with the standard antimalarial treatment. No active follow up will be carried out.

Patients will be assessed as summarized in the following flow-chart.

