#### ***3.10.2. Passive follow up (6 months after the first active follow up)***

Patients identified as treatment failures (clinical and parasitological) within the first follow up of 28 days will be treated with a full course of quinine or any other appropriate oral treatment (unrelated to the study drugs). Parents/guardians of children who have either been treated or classified as ACPR, i.e. with no malaria infection at day 28 of the first follow up will be asked to attend the health facility whenever the child is sick for the next 6 months. Each child will be visited monthly at home to keep the contact with the health facility. However, no data or blood slide will be collected unless the child is sick. Any attendance of children belonging to the cohort recruited for the first follow up will be recorded. The child will be clinically assessed and the medical history will be taken. Body temperature and a blood sample for

parasitaemia, Hb and PCR will be systematically collected. A diagnosis will be made and the child treated accordingly. Whenever an episode of uncomplicated malaria is diagnosed, the inclusion and exclusion criteria (section 3.8) will be checked and if these are fulfilled, the child will be re-treated with the same drug received for the first episode and will be followed up for the next 28 days (second active follow-up) with the same methodology as the first active follow-up. After the second active follow up, even if the child attend with an episode of clinical malaria fulfilling the inclusion/exclusion criteria, s/he will be treated with the local first line drug and no active follow up will be carried out after treatment. Children with a malaria infection but not fulfilling the inclusion and exclusion criteria will be treated with the local first line drug and their parents will be informed that they are still part of the cohort under passive surveillance. Children will reach the end of the study at the end of the 6-month passive follow up when they will be visited at home and the parents/guardians will be informed that the study is finished (Appendix VIII).

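### The day-63 secondary endpoints do not match the planned follow-up: well children have no blood film after day 28, and the six-month stop truncates day 63 for late second episodes

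*Protocol*

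**What the plan says.** - **TF63U.** Section 3.3 adds to the day-28 failures all "recurrent parasitaemias (symptomatic or asymptomatic) detected between day 29 and day 63 by passive follow up", regardless of genotyping.
- **ACPR.** Section 3.2 (end of the late parasitological failure text) sets ACPR equal to one minus the failure proportion, at 28 or 63 days, and words it as a parasitological state: "It is defined as absence of parasitaemia at the end of the follow up period (day 28-63".
- **Sampling after day 28.** The follow-up chart (section 3.8, Figure 1) has its last scheduled film on day 28. In the passive phase each child is visited monthly at home to keep contact (section 3.10.2): "However, no data or blood slide will be collected unless the child is sick". A child who does attend the facility is sampled: blood for "parasitaemia, Hb and PCR will be systematically collected".
- **Second episode.** Section 3.3 lists "TF second clinical episode (D28 and D63" as a secondary endpoint. Section 3.8 allows a second study treatment from day 29: "Re-treatment with the same study drug will be done at an interval of at least 29 days from the first treatment". After the second active phase, "the child will be passively followed up until completion of the 6-month period started at the end of the first active follow up". Section 3.10.2 ends the study at that date. Neither section extends follow-up for late second episodes.
- **End date.** Sections 3.7, 3.8 and 3.10.2 run the six months from the end of the 28-day active phase. The synopsis (Methodology) follows the child "passively until 6 months after treatment".

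**The concern.** Up to day 28 a child who is well but parasitaemic is found by a scheduled film and counted as a late parasitological failure. From day 29 the same child is found only if some illness brings him or her to the facility. TF63U therefore joins two kinds of ascertainment under one label. Its complement, ACPR63, claims a blood status that nobody is scheduled to check.

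The second-episode day-63 endpoint has a separate difficulty. A child whose second episode starts late in the six months reaches the end of the study before day 63. If such a child enters the denominator of a simple proportion with no failure recorded, unobserved time counts as success.

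Both effects lower the reported failure. Efficacy of repeat treatment is part of the main objective and is specific objective 3, so the second-episode result matters although the endpoint is secondary.

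**Working it through.** The protocol gives no share of second episodes with complete day-63 follow-up, so it has no figure of its own to reproduce. The timing of second episodes is not given either. It is assumed below and varied.

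**Inputs**
- Earliest second treatment: day 29 (section 3.8).
- Stop date E, taking six months as 182 days: day 28 + 182 = day 210 (sections 3.7, 3.8, 3.10.2), or day 182 (synopsis).
- Onset window W = E - 28: 182 days, or 154 days on the synopsis date.
- A full day-63 window needs onset no later than E - 63: day 147, or day 119 on the synopsis date.

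**Even onset:** share cut off = 63/W.
- Body of the protocol: 63/182 = 34.6%. With six months as 180 or 183 days it is 35.0% or 34.4%.
- Synopsis date: 63/154 = 40.9%.

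**Constant hazard:** let c be the proportion of children with a second episode within W, and L = -ln(1 - c)/W. The share cut off is [exp(-L(W - 63)) - exp(-LW)] / (1 - exp(-LW)). With W = 182:

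| c | exp(-119L) | minus (1 - c) | divided by c |
|---|---|---|---|
| 0.30 | 0.792 | 0.092 | 30.7% |
| 0.60 | 0.549 | 0.149 | 24.9% |
| 0.90 | 0.222 | 0.122 | 13.5% |

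**Other timings (W = 182):**
- Even onset, but none before day 42 or day 56: 37.3% or 40.6%.
- Incidence rising two- or three-fold across the window: 42.2% or 45.9%.
- Incidence falling to a half or a third: 27.1% or 23.3%.

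Table 1 lists several seasonal sites, so a time trend in either direction is possible.

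**How much time is lost.** Section 3.8 reads as though the second 28-day active phase is completed even when it runs past the six-month date. On that reading, an episode starting u days before the stop loses 63 - max(28, u) days.
- Onset in the last 28 days: 35 days lost each.
- Onset 28 to 63 days before the stop: 17.5 days lost on average.
- Mean among those affected: (28 × 35 + 35 × 17.5)/63 = 1592.5/63 = 25.3 days.
- Mean over all second episodes, even onset: 1592.5/182 = 8.75 days, which is 8.75/63 = 13.9% of planned day-63 observation time. All of it is passive time.

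**First episode.** Day 63 lies well before either stop date, so TF63U for the first episode is not truncated by the calendar. Its weakness is the missing film in well children. The documents do not allow that under-count to be sized.

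**The case against.** The strongest reply is that TF63U is defined by its route of detection. Passive follow-up is part of the definition, and every sick attender is sampled, so parasitaemia without malaria symptoms can be found when a child comes for another illness. This stands. A reader might infer that TF63U cannot be measured, but the text does not support that: it can be computed as passively detected recurrence, with an under-count. The reply does not rescue ACPR63, which is worded as absence of parasitaemia at the end of follow-up.

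A second reply is that incomplete follow-up is a matter for the analysis plan. This stands in part. The protocol nowhere says that truncated children are scored as failure-free. It expects informative missing data and promises sensitivity analyses (section 3.6). But an analysis plan cannot supply films that were not taken or follow-up after the study has ended. The protocol also points towards proportions: ACPR as one minus failure in section 3.2, and an odds ratio for treatment failure in the synopsis.

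A third reply is that the loss is smaller than the share suggests, because only passive days 29-63 are at stake. This stands if the second active phase is completed.

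A reader might also infer that longer-acting drugs are favoured because they push second episodes later. Section 1.1 calls chlorproguanil-dapsone rapidly eliminated and lumefantrine slowly eliminated, so a difference between arms is plausible. The protocol gives no second-episode timing by arm, so neither size nor direction can be claimed.

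**Conclusion.** The mismatch is real and confined to secondary endpoints.

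- ACPR63 as worded is not verified by any planned film in well children. TF63U is measurable but too low as a count of all recurrent parasitaemia, by an amount the documents do not let one derive.
- Second-episode failure at day 63 lacks a full window for about 35% of episodes under even onset over 182 days. The figure is 13.5-30.7% under constant hazard with 90-30% of children having a second episode, and about 41% on the synopsis end date with even onset. About a third is not an upper limit, since late-clustering episodes give more. The lost observation time is about 14% under even onset if the active phase is completed.
- If these endpoints are scored as simple proportions, failure is under-estimated. The shortfall may differ by arm if second-episode timing differs.
- The two end dates contradict each other and must be reconciled.

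TF28U and TF28A for the first episode rest on scheduled films to day 28 and are unaffected, as is the sample size, which is based on day-28 efficacy. The point deserves correction but does not threaten the primary result.

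**What to change.** 1. Label TF63U as day-28 failure plus recurrent parasitaemia detected at illness visits in days 29-63, and do not report ACPR63 as absence of parasitaemia.
2. Analyse second-episode day-63 failure, and TF63U, by time-to-event methods from the relevant treatment date, censoring at the end of follow-up or last contact. Alternatively, restrict the second-episode day-63 endpoint to episodes starting at least 63 days before the end date.
3. State one end date, reconciling the synopsis with sections 3.7, 3.8 and 3.10.2.

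The cost is wording plus an analysis of data already collected, with no extra visits or films. Censoring gives somewhat wider intervals. Restriction drops the late episodes (about 35% under even onset) and describes only the earlier ones. Neither analysis recovers asymptomatic parasitaemia in well children, which is why the relabelling is also needed.

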## 2. TRIAL OBJECTIVES AND PURPOSE

The main objective is to compare the safety and efficacy of 4 artemisinin-based combination therapies (ACT), i.e. amodiaquine-artesunate (AQ+AS), artemether-lumefantrine (AL), dihydroartemisinin-piperaquine (DHAPQ), chlorproguanil-dapsone-artesunate (CDA), for single and repeat treatments of uncomplicated malaria in African children. Safety will be determined by registering adverse events and grading, laboratory, and vital signs evaluations. Their incidence will be compared between the different study arms.

Specific objectives are the following:

1. To evaluate the efficacy of the 4 ACTs for the treatment of children with uncomplicated *P. falciparum* malaria (first active follow-up);
2. To determine after the first active follow-up the incidence rate of a second clinical episode of uncomplicated *P. falciparum* malaria;
3. To evaluate the efficacy of treating the second clinical episode of uncomplicated *P. falciparum* malaria with the same ACT used for the first one (second active follow-up);
4. To evaluate during the active and passive follow up the safety of the 4 ACTs for the treatment of children with uncomplicated *P. falciparum* malaria;
5. To establish the impact of using CDA on the selection of *P. falciparum* genotypes linked to SP resistance.

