### **3.7 Duration of patient follow up**

Each patient will be followed up actively after recruitment for 28 days (first follow up) and then passively for 6 months afterwards. If, within the 6-month period the patient will re-attend the health facility because of clinical malaria, he/she will be actively followed up for 28 days (second follow up) if inclusion and exclusion criteria are fulfilled, otherwise s/he will be treated with the first line drug or any other appropriate antimalarial. From the third episode of clinical malaria onwards, patients will be treated with the first line drug or any other appropriate antimalarial but will not be actively followed up.

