#### ***7.1.5 Length of follow-up for adverse events***

**AEs presenting during the active follow-up period:** A patient still experiencing an AE at the end of the active follow up, i.e. at day 28 will be managed as follows:

- If the AE has been detected and reported before the last visit and
  - it is mild (Grade 1), the patient will be managed according to good medical practice and the active follow up will be stopped. The end date for the AE will be recorded as Day 28.
  - Its grade is more than, the patient will be followed until the AE resolves, improves, or stabilizes.
- If the AE is new, the AE will be reported and the patient will be followed until the AE resolves, improves, or stabilizes.

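### Objective 4 promises safety over active and passive follow-up, but scheduled adverse-event ascertainment covers only the 28 days after each course

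*Protocol*

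**What the plan says.** Objective 4 (protocol section 2, repeated in the synopsis) is "To evaluate during the active and passive follow up the safety of the 4 ACTs". The one safety endpoint, in section 3.3, states that "Subjects will be monitored for 28 days (first and second follow up) for possible development of adverse events". Section 7.1.5, on how long events are followed, has a single branch, headed "AEs presenting during the active follow-up period". It has no counterpart for the passive period.

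Section 3.10.2 describes passive follow-up: "Each child will be visited monthly at home to keep the contact with the health facility". The next sentence reads "However, no data or blood slide will be collected unless the child is sick". The same section then requires every attendance by a cohort child to be recorded, with clinical assessment, history, temperature, a blood sample for parasitaemia, haemoglobin and PCR, and a diagnosis. The study ends with a closing home visit.

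Two general rules also bear on the point. Section 7.1 has the investigator ascertain adverse events at each visit, looking back to the previous one. Section 7.1.3 requires every serious adverse event to be reported within 24 hours and sets no last day.

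**The concern.** The objective and its endpoint cover different periods. The visit procedures in section 3.10.1 include an adverse-event report throughout active follow-up. The passive procedures in section 3.10.2 list what is done at an attendance and do not include one. At a home visit the trigger for collecting data is present sickness. A child who was admitted elsewhere and has recovered, or whose event was treated outside the study facility, is not sick on the day, so nothing in section 3.10.2 prompts the question.

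Safety is half of the main objective. In an open-label trial, events known only through attendance may be ascertained unevenly between arms, and no later analysis can recover events that nobody asked about. A statement about safety over the whole study would rest on two quite different kinds of observation, and the endpoint as worded does not say whether the second kind counts.

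A smaller matter sits in section 7.1.5. A Grade 1 event already reported and still present at the last visit is given Day 28 as its end date, although section 7.1.2 provides an outcome category for ongoing events and section 7.1.4 records a resolution date. The entry reads as a resolution that did not occur.

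**Working it through.** The protocol states no figure for safety coverage, so there is none to reproduce. The check is the share of follow-up time under scheduled adverse-event monitoring.

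**Inputs**
- Monitored time, A: 28 days for one course, 56 days for two (section 3.3; section 3.7 allows at most two active follow-ups).
- Total time, T, on the section 3.7 wording: "Each patient will be followed up actively after recruitment for 28 days (first follow up) and then passively for 6 months afterwards", so T = 28 days + 6 months.
- Total time, T, on the synopsis wording: "Each patient will be actively followed for 28 days and then passively until 6 months after treatment", so T = 6 months.
- 6 months taken as 182.6 days (assumption), varied from 180 to 184.
- A second course does not extend T. Section 3.8 keeps the passive period fixed from the end of the first active follow-up.

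**Formula:** monitored share = A / T; remainder = 1 − A / T.

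| Wording | T (days) | Courses | A / T | Remainder |
|---|---|---|---|---|
| Section 3.7 | 210.6 | 1 | 28 / 210.6 = 13.3% | 86.7% |
| Section 3.7 | 210.6 | 2 | 56 / 210.6 = 26.6% | 73.4% |
| Synopsis | 182.6 | 1 | 28 / 182.6 = 15.3% | 84.7% |
| Synopsis | 182.6 | 2 | 56 / 182.6 = 30.7% | 69.3% |

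Taking 6 months as 180 to 184 days moves each figure by less than one percentage point. The remainder therefore runs from about 69% to 87%.

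**What covers the remainder**
- *Illness attendances (section 3.10.2).* These give real clinical and haemoglobin data, but only when the family attends.
- *Serious-event reporting (section 7.1.3).* It has no end day, but it works only once the site knows of the event.
- *The look-back in section 7.1.* It applies at each visit. For home visits to well children it collides with the no-data rule in section 3.10.2, and sites could settle that conflict differently.

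**The case against.** The strongest reply is that the passive period is under surveillance. Every attendance is recorded with history, haemoglobin and diagnosis, section 7.1 asks about events since the previous visit, serious-event reporting has no cut-off, and section 13.2 has the monitoring board told of serious events during the trials. With monthly contact and a closing home visit, a death or admission would probably come to light. This stands. A reader might infer from the endpoint that most of the safety window is unobserved, or that the trial cannot meet objective 4. The documents support neither. What is missing is scheduled ascertainment, not all observation.

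A second reply is that share of calendar time is not share of safety information. Monitoring is placed straight after each course, repeat treatment gets its own 28 days, and section 1.1 gives half-lives of 24 h and 12 h for chlorproguanil and dapsone, with haemoglobin back to baseline by day 14. Later events are harder to attribute, because other antimalarials are allowed in the passive period. Lighter collection there is a defensible choice, and the percentages should be read as time only. The half-life figures, however, concern one of the four combinations, and section 1.1 itself calls lumefantrine slowly eliminated. In any case, a lighter scheme still has to be stated in the endpoint.

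Third, an arm difference in attendance is a possibility with no figure behind it. That is correct, and no bias is quantified here.

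Fourth, the Day 28 end date affects only Grade 1 events reported before the last visit, the outcome field is recorded separately, and section 3.6 compares numbers and percentages of patients and occurrences, not durations. This also stands. A reader might infer that recorded durations distort a safety comparison, but no stated analysis uses them.

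**Conclusion.** The concern holds as a mismatch of period. Objective 4 spans active and passive follow-up, while the safety endpoint and the event follow-up rule stop at the active periods. About 69% to 87% of follow-up time has no scheduled adverse-event ascertainment and relies on illness attendances and on serious events becoming known to the site.

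The range assumes 6 months is about 183 days, that each active follow-up runs its full 28 days, and that a second one falls inside the window. Section 4.4 stops active follow-up at treatment failure, so the monitored share may be smaller for those children.

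The gap most likely to matter is the serious event managed outside the study facility in a child who has since recovered. Mild events and laboratory changes in children who never attend are also missed, but leaving those out is a reasonable choice if it is stated. This is a cheap improvement to data collection and wording, not a flaw that defeats the safety objective. The Day 28 end date is a data-accuracy correction only.

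**What to change.** 1. **Section 3.10.2:** at the monthly and closing home visits already planned, ask about deaths, hospital admissions and other serious adverse events since the last contact, whether or not the child is sick that day. Record the answers on the existing adverse-event and serious-adverse-event forms.
2. **Section 3.3:** define the safety endpoint as adverse events in the active follow-ups, plus serious adverse events and recorded illness attendances through the end of passive follow-up.
3. **Alternative:** if the extra questions are not wanted, limit objective 4 (section 2 and synopsis) to what is actually collected.
4. **Section 7.1.5 (minor):** record a Grade 1 event unresolved at day 28 with the ongoing outcome from section 7.1.2 and no resolution date.
5. **Synopsis and section 3.7:** reconcile the two wordings for the length of passive follow-up, so that the safety window has one definition.

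The cost is a few questions at visits that already take place, a few lines of protocol text and some additional serious-event paperwork. No new visits, samples or forms are needed, and clinical management does not change.
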